### Interim analyses and stopping guidelines {21b}

Since there are no harmful procedures introduced and adverse effects are unlikely, stopping guidelines are not necessary for this study. Therefore, no interim analyses are planned.

### Methods for additional analyses (e.g. subgroup analyses) {20b}

This trial has four arms. Within each arm, there are no subgroups. Therefore, no additional analyses will be completed.

### Methods in analysis to handle protocol non-adherence and any statistical methods to handle missing data {20c}

Data analysis will be conducted on an intention to treat basis, even if there are cases of protocol non adherence. Study participants will be monitored on a weekly basis for protocol adherence. In between weekly periods, if the study participants need any advice, they have the opportunity to contact the meditation trainer. If any participants are not adhering to protocol, the reasons for not adhering to protocol will be discussed and advice will be provided on how to overcome any difficulties the participants are experiencing in following the protocol. It is not anticipated that there will be much missing data, due to outcome data being collected at patients’ clinic appointments; therefore, multiple imputation of missing data is not warranted. Steps will be taken to understand if data is missing at random, missing completely at random, or missing not at random, and appropriate statistical methods will then be used to handle missing data.

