### Sample size {14}

Sample size was calculated using the WinPepi version 11.65 statistical software. Results from a study by Jeitler et al. [11] with patients with chronic neck pain were used to calculate the sample size. In sample size estimation, we used the standard deviation values of the intervention group (17.2) and the control groups (21.5) after 8 weeks of treatment as stated in the study done by Jeitler et al. [11]. According to this study, the baseline pain value (45.5 SD 23.3) in the intervention group reduced to (21.6 SD 17.2) after 8 weeks of treatment and the baseline pain value (43.8 SD 22) in the control group reduced to (37.7 SD 21.5) after 8 weeks of treatment. Therefore, we considered 17.8 as the minimally important clinical difference. Using these values and a power of 80%, ratio of 1:1 and a significance level of 5%, the sample size was calculated. According to the calculation, the total sample size was 76 and number of patients for each arm of the trial was 19. According to an RCT conducted by Rantonen et al. [25] involving three intervention groups and a control group, the dropout rate was 26%. If we use this 26% dropout rate, and to maintain a total sample of at least 76, we need to have at least 26 patients per each arm of the trial. No adjustments will be made for multiple testing.

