### Study limitations

This is a four-arm parallel clinic-level randomised controlled trial. There can be issues related to clustering effects and allocation concealment. Therefore, allocation to a certain clinic day will be based on availability of sessions rather than patient characteristics, and all patients attending sessions on the relevant days will be systematically invited into the study. The similarity of study participants between intervention groups at baseline will be assessed.

In a randomised controlled trial, patients (or in this case clinic days) are randomly allocated to intervention or control arms. Therefore, patients may receive a meditation intervention that may not be the ideal technique for them personally. In this study, patients will be asked to meditate for at least 15 min/day on their own at home and record the practice duration in a logbook. Therefore, it will not be definitively possible to assess whether the meditation is actually performed or to assess the quality of meditation practised. Other limitations of the study is that analyses may be affected by imbalances between groups at baseline and the limited number of patients in each arm of the trial.

In the present study, expected loss to follow-up is high and potentially puts the study at risk of bias. To reduce dropouts in our study, the patients will be taught about the benefits of regular meditation prior to teaching them meditation. If patients experience any difficulty during their daily meditation practice, they have the facility to discuss them with the meditation instructor

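### Multiple imputation is ruled out because little data will be missing, yet the trial is sized for 26% dropout and calls expected loss high; unless a method is fixed in advance, the intention-to-treat analysis defaults to completers

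*Protocol article*

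**What the plan says.** Three sections of the protocol article bear on how much outcome data will be missing.

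- **Missing data {20c}.** The analysis set is intention to treat: "Data analysis will be conducted on an intention to treat basis, even if there are cases of protocol non adherence". On the amount of missing data: "It is not anticipated that there will be much missing data, due to outcome data being collected at patients’ clinic appointments". From this it concludes: "therefore, multiple imputation of missing data is not warranted". The section ends by saying that the type of missingness will be examined and that "appropriate statistical methods will then be used to handle missing data". No method is named.
- **Sample size {14}.** Before dropout, "the total sample size was 76 and number of patients for each arm of the trial was 19". Enrolment is then raised to a minimum of 26 per arm, for this reason: "If we use this 26% dropout rate, and to maintain a total sample of at least 76".
- **Study limitations.** The article states that "expected loss to follow-up is high and potentially puts the study at risk of bias".

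The section on statistical methods {20a} names two-way ANOVA for change in pain from baseline to week 8, or Kruskal-Wallis if the data are not normal. The regression models in the same section are described as exploratory and as not comparing arms.

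**The concern.** A low expected amount of missing data is the only reason given for excluding multiple imputation, and two other sections deny it. Collecting outcomes at clinic appointments does not help, because a patient who has dropped out does not attend them.

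The consequence reaches the primary outcome. A change score needs a week-8 value, so ANOVA or Kruskal-Wallis on change leaves out every patient who lacks one. If imputation is excluded and nothing is named in its place, the intention-to-treat promise has no method behind it, and the default result is a comparison of those who stayed. With about a quarter of patients expected to leave, any difference in outcome between leavers and stayers can shift the estimated effect.

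The fallback has its own flaw. It presumes that the data can show whether values are missing completely at random, at random or not at random. The last two differ only in how missingness depends on the unobserved values, so no check on observed data can tell them apart.

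**Working it through.** **1. The plan's own figures.** Inputs from Sample size {14}: SDs 17.2 and 21.5, difference 17.8, power 80%, significance level 5% (two-sided assumed, since sidedness is not stated), ratio 1:1, dropout 26%.

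- Root mean square SD = √((17.2² + 21.5²)/2) = √379.05 = 19.47.
- n per arm = 2 × (1.960 + 0.842)² × 379.05 / 17.8² = 18.78, rounded up to 19. Four arms give 76, which matches.
- Dropout: 19 / (1 − 0.26) = 25.7, rounded up to 26 per arm, which also matches. Four arms give 104.

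The arithmetic is sound.

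**2. What the sizing implies about missing data.**

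- Lost per arm: 0.26 × 26 = 6.8, about 7.
- Lost overall: 0.26 × 104 = 27.0.
- Remaining: 0.74 × 104 = 77.0, or 19.2 per arm.

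The patients remaining are almost exactly the 76 on which 80% power rests. By normal approximation, power is 80.5% with 19 per arm and 90.9% if all 26 were observed. The enrolment target therefore makes sense only if those who drop out contribute no final outcome.

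**3. The sections side by side.**

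| Section | Position on missing outcomes |
|---|---|
| Sample size {14} | about 27 of 104 lost |
| Study limitations | loss expected to be high, with risk of bias |
| Missing data {20c} | little expected, so multiple imputation excluded |

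The first two agree. The third conflicts with both, and nothing else in the article reconciles them.

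**4. How far a completers' mean could be off.** The documents give no outcomes for dropouts, so this step is an illustration under an assumption. Let d be the difference in mean change between completers and dropouts in one arm.

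- All-randomised mean = 0.74 × completers' mean + 0.26 × dropouts' mean.
- Error of the completers' mean = completers' mean − all-randomised mean = 0.26 × d.

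| Assumed d (points) | Error in that arm's mean | Share of 17.8 |
|---|---|---|
| 5 | 1.3 | 7% |
| 10 | 2.6 | 15% |
| 17.8 | 4.6 | 26% |

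Points are on the scale of the source study used for sizing. For a comparison of arms A and B, each with 26% loss, the error is 0.26 × (d_A − d_B). It vanishes if dropouts differ from completers equally in both arms, and its sign depends on which arm has the larger difference.

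**The case against.** Four points can be made for the plan.

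- **The 26% is only a cautious allowance borrowed from another trial.** This would carry weight if it stood alone, but the limitations section says of the present study that loss is expected to be high. Nor can the 26% be read as stopping meditation while still attending assessments: the inflation is there to keep at least 76 in the sample, and the limitations section speaks of loss to follow-up. The contradiction stands.

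- **The plan does not prescribe a completers' analysis, and the exact method may be left to a statistical analysis plan.** This is largely right. A reader might infer that a completers' analysis is fixed, but the last sentence of the missing-data section leaves open every method except multiple imputation. Completers are the default, not a stated choice. What remains is more than an omitted detail: the article excludes a named method for a reason it denies elsewhere, and an analysis plan that followed it would inherit the error.

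- **Nothing shows that the method would be chosen after outcomes are seen by arm.** Correct. A reader might infer this from the wording, but no timing is given. The objection to the fallback rests on the mechanism being unidentifiable from observed data, whenever the choice is made.

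- **Nothing shows that meditation would be favoured.** Also correct. It is tempting to argue that patients without benefit leave the meditation arms, which alone carry daily practice and weekly sessions, and that the effect is overstated. The documents give no dropout by arm or by response, and they apply 26% to every arm. Usual-care patients may also have reasons to leave: they know of the other arms and are asked to forgo meditation, yoga and outside treatment. One can construct a 35% overstatement (17.8 among completers against 0.74 × 17.8 = 13.2 for all randomised), but that assumes no benefit at all in every meditation dropout and no matching difference among controls. It is the top row of d in the illustration, divided by 13.2 instead of 17.8, and should not be given as the expected size.

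**Conclusion.** The concern holds in this form: the stated reason for excluding multiple imputation contradicts the article's own planning figure of about 27 of 104 patients lost and its own statement that loss will be high and may cause bias. With only ANOVA or Kruskal-Wallis on change named, the intention-to-treat analysis of the primary outcome defaults to completers unless a method is fixed in advance. Diagnosing the mechanism from the data is not a workable substitute.

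The size of any bias is unknown and its direction is open. The range of 1.3 to 4.6 points rests on 26% loss in one arm and on assumed completer-dropout differences of 5 to 17.8 points. It carries over in full to a between-arm comparison only if dropouts in the other arm resemble its completers. The sample-size arithmetic is not at fault.

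**What to change.** Before outcomes are analysed:

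1. Reconcile Sample size {14}, the missing-data section {20c} and Study limitations so that all three state the same expected loss.
2. Delete the statement that multiple imputation is not warranted, and the plan to choose a method from a diagnosed mechanism.
3. Pre-specify one primary method valid under missing at random that uses the pain data already collected at weeks 4, 8 and 12. It can be a likelihood-based repeated-measures model with arm by visit and baseline as covariate, or multiple imputation that includes the other visits. The model uses patients with at least one follow-up value. Imputation also keeps those with none, which is closer to the intention-to-treat promise.
4. Add one pre-set missing-not-at-random sensitivity analysis, such as control-based imputation or a range of fixed shifts for dropouts. This is needed because neither method in step 3 would by itself correct bias from dropouts whose unobserved outcomes differ in ways their earlier data do not show.

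The cost is revised wording and modest extra analysis work. No new data collection and no change in enrolment are needed.

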### Plans to give access to the full protocol, participant-level data and statistical code {31c}

When the trial results are published, an anonymised version of the dataset will also be provided as a supplementary file. Confidential data related to the trial participants will not be provided.

## Oversight and monitoring

### Composition of the coordinating centre and trial steering committee {5d}

The trial will be handled by the three researchers who will meet once every 2 weeks to assess how the trial is running. In addition, there will be a physician and physiotherapist involved in the routine treatment of patients. The meditating instructor will train the participants in the meditation techniques, while another therapist will assess the outcomes. Allocating patients to usual care control and intervention arms and registering patients will be carried out by a nursing assistant. Data entry will be conducted by a research assistant.

### Composition of the data monitoring committee, its role and reporting structure {21a}

Data monitoring will be conducted by the research team on a monthly basis.

### Adverse event reporting and harms {22}

The interventions do not include any harmful procedures. Therefore, adverse events are unlikely. If due to a rare chance an adverse effect occurs, it will be notified to the ISRCTN trial registry and also to the University of Bath Ethics committee.

### Frequency and plans for auditing trial conduct {23}

There are no harmful procedures introduced in this trial and adverse effects are unlikely. Therefore, there is no formal data monitoring committee. However, at the time that outcome data are assessed, a clinician who is independent of the trial team will monitor data analyses.

### Plans for communicating important protocol amendments to relevant parties (e.g. trial participants, ethical committees) {25}

At present, we do not feel any protocol amendments are required. However, if any important protocol amendments are done, it will be notified to the University of Bath Research Ethics Approval Committee for Health, ISRCTN trial registry and the participants.

### Dissemination plans {31a}

We intend to publish the trial results in peer-reviewed scientific journals and present these at scientific conferences. There are no publication restrictions.

## Discussion

The prevalence of work-related complaints of neck and shoulder among office workers in Sri Lanka is high (63.6%) [28], and comparable to the prevalence in developed countries (30–70%) [2, 29]. Most cases of neck and shoulder region pain are due to poor posture while at work [28]. In Sri Lanka, the retirement age is 65 years. Therefore, most patients affected with neck and shoulder region pain in Sri Lanka due to posture-related causes can be detected under the age of 65 years. So, exclusion of participants over the age of 65 years is unlikely to affect the generalisability of the data. Sri Lankan patients, similar to patients in other countries, prefer treatments that are low cost, with less side effects, and are easy to comply with [17].

Meditation has minimal or no negative side effects and the effect of meditation on easing pain and disability has not been studied in Sri Lanka. Comparing three meditation techniques with a usual care control group and with each other on pain, physical disability and psycho-social disability has not been described in previous literature. Therefore, conducting this study will contribute toward filling gaps in knowledge in this area of research. It may also evidence a treatment technique which is low-cost and less time consuming for managing patients who are affected with chronic neck and shoulder region pain in Sri Lanka. As a future study, to assess the robustness of findings, additional populations may be used.

### Study limitations

This is a four-arm parallel clinic-level randomised controlled trial. There can be issues related to clustering effects and allocation concealment. Therefore, allocation to a certain clinic day will be based on availability of sessions rather than patient characteristics, and all patients attending sessions on the relevant days will be systematically invited into the study. The similarity of study participants between intervention groups at baseline will be assessed.

In a randomised controlled trial, patients (or in this case clinic days) are randomly allocated to intervention or control arms. Therefore, patients may receive a meditation intervention that may not be the ideal technique for them personally. In this study, patients will be asked to meditate for at least 15 min/day on their own at home and record the practice duration in a logbook. Therefore, it will not be definitively possible to assess whether the meditation is actually performed or to assess the quality of meditation practised. Other limitations of the study is that analyses may be affected by imbalances between groups at baseline and the limited number of patients in each arm of the trial.

In the present study, expected loss to follow-up is high and potentially puts the study at risk of bias. To reduce dropouts in our study, the patients will be taught about the benefits of regular meditation prior to teaching them meditation. If patients experience any difficulty during their daily meditation practice, they have the facility to discuss them with the meditation instructor

## Trial status

Initial Protocol version numbers were 01 and date 08.03.2022; 02 and date 10.08.22.

Amended Protocol version number is 03 and date 21.09.2022.

At the time this protocol paper was submitted, recruitment had not begun due to the COVID-19 pandemic situation in Sri Lanka. We anticipate that it will take 1 year to recruit and an additional 3 months to complete the monitoring. By the time we received reviewer comments on the manuscript, recruitment had started (recruitment start date: 18/04/2022).

## Data Availability

The data will be accessible only by the three authors. On completion of the study, data will be stored in University of Bath Data Archive.

## Abbreviations

DASH: Disability Arm, Shoulder and Hand
SF-36: Short Form 36
